### Study outcomes

Primary and secondary endpoints are presents in Table 2. The outcomes of the migraine changes are adjudicated based on the headache diary data. The total days of migraine is defined as migraine frequency per month plus migraine average duration, divided by 24, round up to nearest integral. The definition of responder rate is the percentage of patients who have at least 50% reduction of monthly migraine attacks from their baseline. Other efficacy measures include migraine severity, as assessed by the HIT-6 scale [17], and quality of life alterations, determined by the SF-36v2 questionnaire [18]. These changes would be also analyzed the relationship with a successful PFO closure and residual shunt.

**Table 2 Tab2:** Primary and secondary endpoints

Primary endpoint
Complete cessation of migraine during the follow up.
Secondary efficacy endpoints
Mean reduction of monthly migraine attacks. Mean reduction of monthly migraine days. Responder rate.
Secondary safety endpoints
All-cause mortality. Peripheral embolism. New-onset arrhythmia warranting intervention. New-onset myocardial infarction. Other complications related to PFO closure procedure, device and antiplatelet drugs. Other side effects associated with the drugs used in the study.

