### Sample size and statistical considerations

This was a randomized controlled study with PFO blocking group as the intervention group and drug treatment group as the control group. Migraine frequency (monthly migraine days), improvement in migraine frequency, severity (migraine scale score) and quality of life score were the outcome indicators. According to previous reports, the frequency of migraines treated with medication was 6.5 ± 2.4 days/month. The migraine HIT-6 score was 66.2 ± 5.1; After treatment, the number of migraine attacks per month can be reduced by 25%; SF12 quality of life score increased by 1.2 ± 6.9 points after treatment. The frequency of migraine was expected to decrease by 0.6 days in PFO occlusion group. Migraine scale HIT-6 score decreased by 1.5 points; After treatment, the number of migraine attacks per month can be reduced by 50%; SF12 quality of life score improved by 4.2 points after treatment. The test level was set as bilateral α = 0.05, and the assurance was 80%. PASS 15.0 software was used to calculate the required sample size of 113, 183, 60 and 156 cases in each group based on the above four observation indicators. Taking the maximum sample size and considering 20% of the cases of loss and refusal to visit, the final requirement was 220 cases in the PFO blocking group and 220 cases in the drug treatment group.

The primary endpoints will be analyzed across different analysis sets: Intention-to-Treat, per-protocol, and as-treated, with the primary analysis set being Intention-to-Treat. Categorical variables will be described using rates and composition ratios. Group differences in variables such as migraine termination, sociodemographic factors, migraine incidence rate, changes in migraine characteristics (with or without aura and their changes), effective closure rates, or residual leakage will be compared using the chi-square test. Continuous variables will be characterized based on their data distribution, utilizing means, standard deviations, medians, and interquartile ranges. Group differences in variables such as sociodemographic factors, severity and frequency of migraine attacks, and quality of life scores derived from the SF-36v2 questionnaire will be compared using t-tests or the Wilcoxon test.

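### Two of the four stated sample sizes do not follow from their own inputs: migraine days needs about 252 per group where 113 is printed, and quality of life about 84 where 156 is printed

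*Protocol article*

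**What the plan says.** All of the sizing is in the section Sample size and statistical considerations of the protocol article. The error rates are given as "The test level was set as bilateral α = 0.05, and the assurance was 80"%. The inputs are:

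- **Monthly migraine days.** Control: "the frequency of migraines treated with medication was 6.5 ± 2.4 days/month". Closure: "The frequency of migraine was expected to decrease by 0.6 days in PFO occlusion group".
- **HIT-6.** Control: "The migraine HIT-6 score was 66.2 ± 5.1". Closure: a fall of 1.5 points.
- **Attacks per month.** A 25% reduction on medication and 50% after closure, with no SD.
- **Quality of life.** Control: "SF12 quality of life score increased by 1.2 ± 6.9 points after treatment". Closure: "SF12 quality of life score improved by 4.2 points after treatment".

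From these the article reports "the required sample size of 113, 183, 60 and 156 cases in each group based on the above four observation indicators". It takes the largest, allows 20% for loss to follow-up, and arrives at 220 per group. Table 2 lists the mean reduction in monthly migraine days as a secondary efficacy endpoint. Under Study outcomes the quality-of-life measure is described differently from the sizing paragraph: "quality of life alterations, determined by the SF-36v2 questionnaire".

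**The concern.** Inputs and results are printed in the same paragraph, so each size can be checked directly. Migraine days has a standardised difference of 0.6/2.4 = 0.25, and HIT-6 has 1.5/5.1 = 0.294. The smaller standardised effect must need more patients, yet the article gives migraine days 113 and HIT-6 183. Quality of life has the largest standardised difference of the three (3.0/6.9 = 0.435) and should need the fewest, yet it is given 156.

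The final size is the maximum of the four, so a figure that is too low can hide the outcome that should have set it. A reader would take it that migraine days has at least 80% power for the stated difference, and could over-interpret a null result on that endpoint. The Discussion raises the stakes: it names small samples as a possible reason why the earlier randomised trials missed their endpoints, and offers a larger sample as a remedy.

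**Working it through.** **Inputs** (all from the sample-size section): two-sided α = 0.05; power 0.80; equal groups; differences and SDs as listed. The quality-of-life difference is 4.2 − 1.2 = 3.0.

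**Formula.** For two means, the normal approximation is n per group = 2(1.960 + 0.842)² (SD/δ)² = 15.70 (SD/δ)². The exact two-sample t-test adds about one patient.

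**Step 1: reproduce the plan's figure that works.** HIT-6: 15.70 × (5.1/1.5)² = 181.5, so 182. The t-test gives 182.4, so 183. This matches the printed figure and indicates the method used.

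**Step 2: apply the same method to the other two means.**

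| Outcome | δ | SD | Normal approximation | t-test | Printed |
|---|---|---|---|---|---|
| HIT-6 | 1.5 | 5.1 | 182 | 182.4 → 183 | 183 |
| Migraine days | 0.6 | 2.4 | 252 | 252.1 → 253 | 113 |
| Quality of life | 3.0 | 6.9 | 84 | 84.01 → 85 | 156 |

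Migraine days is too small by a factor of 252/113 = 2.2. Quality of life is too large by 156/84 = 1.9.

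**Step 3: look for another method that gives the printed sizes.**

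- Migraine days: one-sided test 198–199; paired or one-sample 128; one-sided paired 101; Wilcoxon inflation 265–293. None gives 113.
- A smaller SD in the closure group cannot rescue 113. With control SD 2.4, the closure variance would have to be 113 × 0.6²/7.849 − 2.4² = −0.58, which is impossible.
- 113 would need a pooled SD of about 1.6, or a baseline correlation of about 0.74 in a covariance analysis. Neither is stated.
- Quality of life: 90% power 112–113; one-sided 66–67; Wilcoxon 90–99; reading 4.2 as the difference 43–44. None gives 156, which would need a pooled SD of about 9.4.

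**Step 4: solve back from the printed sizes.** With SD 2.4, n = 113 detects 0.898 days; 0.9 days needs 112.6, so 113. With SD 6.9, n = 156 detects 2.196 points; 2.2 points needs 155.4, so 156. Neither 0.9 nor 2.2 appears in the article.

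**Step 5: power for 0.6 days with SD 2.4 (t-test).**

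| n per group | Basis | Power |
|---|---|---|
| 113 | printed for this outcome | 46% |
| 176 | 220 less 20% | 65% |
| 183 | adopted maximum | 66% |
| 220 | no loss | 74% |

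**Step 6: the fourth size.** Treating 25% and 50% as proportions of patients gives 57.7 (pooled variance), 54.9 (unpooled) or 65.4 (continuity-corrected). The printed 60 is close to the first but is not hit exactly. As worded, these are percentage reductions in attack counts with no SD, from which no size can be computed.

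**The case against.** The mismatch itself is not in dispute. The strongest counter-argument concerns its direction. Two exact matches at one-decimal differences (0.9 and 2.2) suggest that the software was given those values and that the article misprints the inputs. If 0.9 days was used, 183 is the true maximum and power for migraine days is about 94% at 176 per group. This stands as a possibility. It means that 252, and the power figures of 46% to 74%, hold only if the printed 0.6 days and SD 2.4 are right. It does not remove the error, because the paragraph is then wrong in its inputs.

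Second, the SD of 2.4 belongs to a monthly level, while the endpoint is a reduction, and the protocol mentions covariance analysis. If that analysis adjusted for baseline, a correlation of about 0.55 would bring the requirement to 252 × (1 − 0.55²) ≈ 176. The article states neither the adjustment for baseline nor a correlation, so this cannot support the printed 113, which would need about 0.74.

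Third, the consequence is bounded. Migraine days is a secondary endpoint, the adopted 183 does reproduce from HIT-6, and the quality-of-life figure errs on the safe side without affecting the maximum. All of that is correct. That taking the maximum is meant to secure 80% power for every indicator is also an inference, though the natural one. The SF-12 wording and the loose fit to 60 are reporting points and carry little weight here.

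**Conclusion.** The concern holds. Two of the four printed sizes contradict the inputs printed beside them, and no method described in the article reconciles them. On the stated inputs (two-sample t-test, two-sided 0.05, 80% power), migraine days needs 252 to 253 per group against 113, and quality of life 84 to 85 against 156. If 0.6 days with SD 2.4 is what the investigators intend, 183 is not the maximum, and 220 per group gives 65% to 74% power for that secondary endpoint, depending on loss between 20% and none. If 0.9 days and 2.2 points were the differences used, the sizes are sound and the printed inputs are wrong. The article alone cannot decide between these, but it is wrong as written in either case.

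**What to change.** Reconcile inputs and sizes in the sample-size paragraph:

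1. **Migraine days.** Either print the difference actually used (0.9 days, if so), or restate the size as 252–253 per group. If 0.6 days stands, keep 220 per group and state the power for this endpoint as 65% with 176 evaluable and 74% with 220.
2. **Quality of life.** Either print the difference used (2.2 points, if so), or restate the size as 84–85. Restate the input for SF-36v2, since that is the instrument the trial collects.
3. **Attacks.** If the 25% and 50% were entered as responder proportions, describe them so.

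The cost is a correction to one paragraph. Enrolment does not change. If 0.6 days is kept, one stated power figure becomes less favourable.

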### Follow up

Follow-up assessments will be conducted at 1, 3, 6, and 12 months post-intervention. These will include the recording of migraine diaries, completion of questionnaires assessing migraine impact, quality of life, medication history, and any serious adverse events. At the 6 and 12-month marks, or upon reaching the primary endpoint, additional follow-up assessments will be conducted. These will consist of TTE/TEE with right heart contrast and TCD with a bubble test to re-evaluate the right-to-left shunt. When adverse events are identified during follow-up, investigators will assess the condition and severity to determine whether to terminate the trial.

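### The continuous secondary outcomes are recorded at four visits with 20% loss expected, yet are compared by one-value-per-patient tests at no stated time point

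*Protocol article*

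**What the plan says.** All references are to the protocol article.

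- **Loss.** Under Sample size and statistical considerations, the largest of the four per-arm sizes ("required sample size of 113, 183, 60 and 156 cases in each group based on the above four observation indicators") is enlarged "considering 20% of the cases of loss and refusal to visit", and "the final requirement was 220 cases in the PFO blocking group and 220 cases in the drug treatment group".
- **Test.** The same section states that "quality of life scores derived from the SF-36v2 questionnaire will be compared using t-tests or the Wilcoxon test". The sentence also covers the severity and frequency of attacks; Study outcomes measures severity by HIT-6.
- **Visits.** Follow up states: "Follow-up assessments will be conducted at 1, 3, 6, and 12 months post-intervention". Diaries and the impact and quality-of-life questionnaires belong to these assessments.
- **Endpoints.** Table 2 lists the mean reductions in monthly attacks and in monthly migraine days, and the responder rate, as secondary efficacy endpoints. It attaches no month to any of them.
- **Further models.** The statistical section adds covariance analysis, generalized linear models with centre as random effect, and Kaplan–Meier and Cox methods.
- **Analysis sets.** They are introduced for the primary endpoints, "with the primary analysis set being Intention-to-Treat".

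**The concern.** A two-sample t-test or Wilcoxon test needs each patient reduced to one number. With four scheduled visits and a fifth of patients expected to be lost, that reduction decides who is compared and on what, and the article does not say how it is made.

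The trial is open-label, and Study protocol and PFO device closure give both arms the same antiplatelet course. A control patient without relief could therefore have more reason to leave than a closure patient. If loss follows lack of improvement and is heavier among controls, the controls who remain look better than those randomised, and a completers' comparison understates the closure effect. Two of the three secondary efficacy endpoints are exposed, as are HIT-6 and SF-36v2.

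**Working it through.** **1. The plan's own figures.** HIT-6 drives the size: "The migraine HIT-6 score was 66.2 ± 5.1", so SD 5.1, with an expected decrease of 1.5 points, two-sided α 0.05 and 80% power. The exact t-test calculation gives 182.4, rounded up to 183 per arm, as stated. Then 183 × 1.2 = 219.6, rounded up to 220, also as stated.

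**2. Loss of precision.** 20% of 220 is 44 per arm (88 of 440), leaving 176 per arm with complete data.

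| Analysed per arm | HIT-6 power (1.5, SD 5.1) | Migraine-day power (0.6, SD 2.4) |
|---|---|---|
| 220 | 87.0% | 74.6% |
| 183 | 80.3% | 66.7% |
| 176 | 78.8% | 65.0% |

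**3. What earlier visits would recover.** Suppose the lost patients have one earlier visit whose correlation with the final value is ρ. The effective size is 176 / (1 − 0.20 × ρ²). The article gives no ρ, so a range is shown.

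| ρ (assumed) | Effective n per arm | HIT-6 power |
|---|---|---|
| 0.3 | 179 | 79.5% |
| 0.5 | 185 | 80.8% |
| 0.7 | 195 | 82.8% |
| 0.8 | 202 | 84.0% |

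**4. Bias on HIT-6, simple formula.** If lost patients are k SDs worse than those who stay, the bias is k × SD × (control loss − closure loss). The split by arm and k are assumptions.

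- k = 0.5, 25% v 15%: 0.5 × 5.1 × 0.10 = 0.26 points.
- k = 0.5, 30% v 10%: 0.5 × 5.1 × 0.20 = 0.51 points.
- Equal loss with the same pattern in both arms: 0.

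The target difference is 1.5 points.

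**5. Bias on migraine days, simulation.** From the article: 220 per arm, SD 2.4, difference -0.60, visits at 1, 3, 6 and 12 months. Assumed: adjacent-visit correlation 0.5 or 0.7; patients leave before month 3, 6 or 12; where loss is outcome-driven, it depends on change from baseline at the last visit. In the controls-only scenario about 28–30% of controls are lost, against 14–15% of closure patients, at random. Two separately coded simulations (1,500 and 500 replicates) gave these month-12 estimates:

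| Scenario | Method | Estimate (truth -0.60) |
|---|---|---|
| Random, equal loss | Completers' t-test on change | no bias |
| Same outcome-driven loss in both arms | Completers' t-test on change | -0.50 to -0.55 |
| Outcome-driven in controls only, correlation 0.5 | Completers' t-test on change | -0.09 and -0.12 |
| Outcome-driven in controls only, correlation 0.7 | Completers' t-test on change | -0.26 and -0.29 |
| Outcome-driven in controls only | Completers' ANCOVA | -0.39 to -0.41 |
| Outcome-driven in controls only | Likelihood estimate from all visits | -0.60 to -0.61 |

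**6. Do the other stated methods use the visits?** The only random effect described is centre. Without a patient-level effect or within-patient correlation, the covariance and generalized linear models as described also work on one value per patient. Kaplan–Meier and Cox deal with incomplete follow-up only for time-to-event outcomes.

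**The case against.** Several counter-arguments carry weight.

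- **No final value is fixed.** A reader might infer that only patients with a month-12 value can be scored. The article does not say so: the single value could be an average over available diary months, or an imputed value, and some lost patients would stay in. This stands. Averaging brings its own problem, since a patient followed for three months and one followed for twelve then count as like for like.
- **No breach of Intention-to-Treat is shown.** A reader might infer a contradiction with the primary analysis set. The article ties the sets to the primary endpoints, and Table 2 lists only complete cessation as primary. It makes no such commitment for these outcomes.
- **Missing-data rules may be in the analysis plan.** The lack of an imputation rule in a condensed article is no finding, and the 20% allowance is a sizing device that does not say lost patients will be excluded. The point rests on the method that is stated.
- **The size of the bias comes from the assumed mechanism.** A reader might take -0.09 as the expected result. It needs outcome-driven loss in one arm only, and the article gives neither a split by arm nor the timing of loss. At correlation 0.5, ANCOVA moves the estimate from -0.09 to -0.39, so about 0.30 of the 0.51 shortfall comes from unadjusted change scores, and covariance analysis is among the planned additional analyses. The all-visit method recovers -0.60 partly by design, because simulated loss depends only on observed values and every patient has a month-1 visit.

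**Conclusion.** The point holds as a worthwhile, inexpensive improvement to the analysis of the continuous secondary outcomes. The stated tests suit poorly the four-visit data the trial collects and the loss it expects, and the additional models as described do not repair this.

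The precision cost alone is minor: HIT-6 power of 78.8% against the planned 80%. The reason to act is possible bias, whose size is unknown. It is nil under random equal loss, modest if the same mechanism acts in both arms, and large only if loss is outcome-driven and confined to controls. That last case is an assumption made plausible by the open-label design, not something the article states. The point does not touch the cessation endpoint.

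**What to change.** Under Sample size and statistical considerations, make the main comparison of monthly attacks, monthly migraine days, HIT-6 and SF-36v2 a mixed model for repeated measures. It should use all recorded visits of all randomised patients, with baseline value, treatment, visit and treatment-by-visit as fixed terms, within-patient correlation across visits, and centre as random effect as already planned. State the visit at which the treatment contrast is reported. Add one sensitivity analysis that departs from missing at random, for example one giving lost closure patients the control-arm trajectory. Settle this before the analysts see outcomes by arm.

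The cost is analysis-plan wording and a little more programming; no new data, visits or patients are needed. The downside is reliance on missing at random, which the sensitivity analysis probes but cannot remove. Patients with no post-baseline data still do not contribute.

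### The 20% loss allowance was applied by multiplying by 1.2 rather than dividing by 0.8, so 220 per group leaves 176 evaluable, 7 short of the 183 the plan requires

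*Protocol article*

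**What the plan says.** All the figures are in one paragraph of the protocol article, under Sample size and statistical considerations.

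- Error rate and power: "The test level was set as bilateral α = 0.05, and the assurance was 80" per cent.
- The paragraph gives planning values for four outcomes and reports a "required sample size of 113, 183, 60 and 156 cases in each group based on the above four observation indicators". The largest, 183, is the HIT-6 figure, based on "The migraine HIT-6 score was 66.2 ± 5.1" and an expected effect given as "Migraine scale HIT-6 score decreased by 1.5 points".
- The last step starts from that largest figure ("Taking the maximum sample size") and reads: "considering 20% of the cases of loss and refusal to visit, the final requirement was 220 cases in the PFO blocking group". The drug group gets the same number, 440 in total.

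The inflation formula is not written out. Nothing elsewhere in the article revises the loss rate, the 183 or the 220.

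**The concern.** A loss allowance should leave the required number of evaluable patients after the expected losses. Losses come out of the patients enrolled, so the target has to be divided by the retained fraction. Multiplying the target by one plus the loss rate takes the percentage of a smaller base and falls short. At 20% the retained share of the target is 1.2 × 0.8 = 0.96, so before rounding the method always ends 4% below the number it was meant to protect.

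Here the required number, the loss rate and the final size are all printed, and the three do not agree. What is at stake is whether 220 per group gives 80% power at the attrition the plan itself expects, and whether those monitoring retention know how much loss the trial can absorb. The Discussion suggests that small samples may have contributed to earlier trials missing their endpoints and offers a larger sample as part of the remedy, so the margin should be stated correctly.

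**Working it through.** **Inputs**, all from Sample size and statistical considerations: two-sided α = 0.05; power 80%; HIT-6 SD 5.1; HIT-6 difference 1.5; pre-loss maximum 183 per group; loss 20%; final size 220 per group.

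**1. Reproduce the 183.** For two means with equal allocation,

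n = 2 (z₀.₉₇₅ + z₀.₈₀)² (SD/δ)² = 2 × (1.960 + 0.842)² × (5.1/1.5)² ≈ 15.70 × 11.56 ≈ 181.5, so 182 per group.

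The t-test version gives 182.4, rounded up to 183. The plan's figure reproduces.

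**2. Reproduce the 220.**

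| Rule | Calculation | Per group |
|---|---|---|
| Multiply by 1 + loss | 183 × 1.2 = 219.6 | 220 |
| Divide by 1 − loss | 183 / 0.8 = 228.75 | 229 |

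Of the two usual rules, only multiplication gives 220. Division differs by 9 patients per group (18 in total), which is too much for rounding.

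**3. What 220 leaves at 20% loss.** 220 × 0.8 = 176 per group, which is 183 − 176 = 7 short. By comparison, 229 × 0.8 = 183.2.

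**4. The loss that 220 can absorb.** 1 − 183/220 = 37/220 = 16.8%.

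**5. Power for HIT-6 (δ = 1.5, SD 5.1, two-sided 0.05).**

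| Evaluable per group | Normal approximation | t-test |
|---|---|---|
| 183 | 80.3% | 80.1% |
| 176 | 78.8% | 78.6% |

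The normal approximation at 176: 1.5 / (5.1 × √(2/176)) = 2.759; 2.759 − 1.960 = 0.799; Φ(0.799) = 0.788. The cost is about 1.5 percentage points.

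**The case against.** **The wording could mean a 20% add-on.** The article prints no formula. If the intention was to add 20% of 183 as extra patients, 220 is exact. But the sentence ties the 20% to patients lost or refusing visits, which is naturally a share of those enrolled. Even as an add-on, the loss covered is 16.8%, and the text should say so.

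**Lost patients may still contribute.** The primary analysis set is Intention-to-Treat, and the section also plans Kaplan–Meier and Cox analyses, in which partly followed patients count. That is fair for time-to-event outcomes. It does not produce a follow-up HIT-6 score for someone who stops attending, and HIT-6 is the outcome that sets the 183. Covariance adjustment could recover the gap: assuming a covariate correlated with HIT-6 at about r = 0.20, r² ≈ 0.04 matches 1 − 176/183 = 0.038. It is planned only as an additional analysis and is not part of the sample-size calculation, but it does show how small the shortfall is.

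**The shortfall does not touch a listed endpoint.** In Study outcomes, HIT-6 is among the other efficacy measures, whereas Table 2 makes complete cessation primary and lists attacks, migraine days and responder rate as secondary. On the sizes the plan states for its other three indicators (113, 60 and 156), 176 is still enough. This stands, and it limits the consequence. No cessation rates are given from which an effect on the primary comparison could be worked out.

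**The base number has problems of its own.** Also true, and larger. The printed inputs for migraine days (difference 0.6, SD 2.4) give 2 × (1.960 + 0.842)² × (2.4/0.6)² ≈ 251.2, i.e. 252 per group rather than 113, and none of the four sizing outcomes is the primary endpoint. Those are separate matters. If the base is re-derived, 229 and 16.8% will change with it, but division by 0.8 remains the right step for a 20% loss.

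**Conclusion.** The concern holds. At the plan's own 20% loss rate, 220 per group leaves 176 evaluable patients against a stated need of 183: 7 evaluable, or 9 enrolled, too few in each group. HIT-6 power is then 78.6% rather than 80%, and 220 keeps the target only up to 16.8% loss.

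This rests on three things: taking 183 as the plan's stated requirement; reading the 20% as the share of enrolled patients who give no usable follow-up score; and the printed HIT-6 difference and SD. That multiplication was the rule used is inferred from the numbers, since the formula is not shown, but the shortfall itself follows directly from the printed 183, 20% and 220.

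The error is certain but modest. It does not undermine the design; it makes the stated attrition margin and power wrong as written.

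**What to change.** Keep 220 per group and correct the statement, for example: 220 per group allows for 16.8% loss while retaining 183 evaluable patients; at 20% loss (176 per group) the power for HIT-6 is 78.6%. This costs one sentence and no additional patients.

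If a 20% allowance is to be kept as a requirement, the size becomes 229 per group (458 in total), 18 more patients than planned.

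Either way, write out the formula, N / (1 − loss), so that the same step is applied correctly if the base number is revised.

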### Study design

The Spring study is a multicenter, randomized and open-label trail comparing the effectivity and safety of PFO closure vs medicine in alleviating migraine, with a follow-up period of 12 months (ClinicalTrials.gov ID NCT04946734). The trial is performed in 21 centers in China and has been approved by all local ethics committees. Our hypothesis posits that, compared to medication alone (clopidogrel 75 mg q.d. and aspirin 100 mg q.d.), PFO closure accompanied by one months of clopidogrel (75 mg q.d.) and six months of Aspirin (100 mg q.d.) will be more effective in completely ceasing migraines. Patient recruitment is expected to be completed by the end of 2024, with final results anticipated in 2025.

Patients with migraine and PFO were included in this study. Participant inclusion and exclusion criteria are presented in Table 1.

**Table 1 Tab1:** Inclusion and exclusion criteria

Inclusion criteria
1. Subject is aged between 16 and 60 years old.
2. Subject is diagnosed of PFO with right-to-left shunt, confirmed by Transthoracic echocardiography (TTE) or transesophageal echocardiography (TEE) with agitated saline contrast.
3. Subject is diagnosed of right-to-left shunt, confirmed by transcranial doppler with agitated saline contrast.
4. Subject is diagnosed of migraine without identifiable cause of headache.
5. Subject signs an informed Consent Form and is willing to participate in follow-up visits; 6. Primary and secondary endpoints.
Exclusion criteria:
1. Subject is diagnosed of headache with clear etiology.
2. Subject had cerebral hemorrhage, bleeding events in other organs within 3 months or was in high risk of bleeding.
3. Subject presents with ischemic lesions as indicated by brain CT/MR imaging.
4. Subject is diagnosed of hepatic insufficiency: ALT or AST > 3 × ULN at the screening visit.
5. Subject is diagnosed of moderate to severe renal insufficiency: eGFR < 30 ml/min/1.73m2 at the screening visit.
6. Subject has uncontrolled arrhythmia with clinical significance within 90 days.
7. Subject is diagnosed of unstable angina, severe coronary atherosclerosis or myocardial infarction within 90 days.
8. Subject is diagnosed of pulmonary artery embolism, peripheral artery embolism or deep Vein Thrombosis.
9. Subject cannot follow the study procedure due to other acute or chronic diseases.
10. Subject is pregnant or lactating.
11. Subject is under other RCT.
12. Subject has a life expectancy < 1 year.

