Additional analysis will involve covariance analysis to account for factors significantly influencing the observed indicators. Different centers will be treated as random effects, and generalized linear models will be employed to further control for the potential impact of center effects. Stratified analysis will be performed based on factors such as gender and age. Predefined subgroups will include migraine with or without aura. Survival function estimation will be conducted using the Kaplan–Meier method. Relevant covariates will be controlled for using the Cox proportional hazards model, and truncated data will be analyzed accordingly.

For all analyses, a two-tailed *P* value < 0.05 was used as the criterion for statistical significance. Analyses were performed using SPSS 22 software (IBM Corp., Armonk, NY, USA).

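### The adjusted analysis leaves covariates to be chosen by significance and the continuous outcomes are tested unadjusted; a prespecified baseline ANCOVA would close that choice and gain power at almost no cost

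*Protocol article*

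**What the plan says.** The section Sample size and statistical considerations describes two layers of analysis.

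- **Main comparisons.** Migraine termination and other categorical variables are compared by chi-square. For the continuous outcomes, which include severity and frequency of attacks, the text reads: "quality of life scores derived from the SF-36v2 questionnaire will be compared using t-tests or the Wilcoxon test". No covariate is named for any of these tests.
- **Further analyses.** "Additional analysis will involve covariance analysis to account for factors significantly influencing the observed indicators". The text gives no candidate list and no threshold. Centre is to be a random effect, with generalized linear models to control for it. Stratified analyses by factors such as sex and age, a predefined aura subgroup and a Cox model with unnamed covariates follow. Every analysis is judged at two-sided P < 0.05.

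Under Study outcomes, two secondary efficacy endpoints are mean reductions (monthly attacks, monthly days). The third, responder rate, is a reduction of at least 50% from baseline. Baseline values are therefore needed in any case.

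**The concern.** Two features of the text pull against a clean analysis.

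First, the covariance sentence makes observed significance the ground for including a covariate. The adjusted model is then unknown until the outcomes have been seen. In an open-label trial with patient-kept diaries and several supplementary models, all at 0.05, this adds one more free choice. A later plan that named its covariates in advance would conflict with this sentence, so the sentence itself needs to change.

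Second, the trial will hold baseline values for migraine days and attacks but makes no use of them as covariates. For the reduction endpoints, baseline enters only by subtraction. That is less efficient than regression on baseline and, at low correlation, worse than ignoring baseline altogether. What is at stake is power on the continuous secondary outcomes, and how far a reader can trust an adjusted estimate.

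**Working it through.** **Inputs from the article.** Two-sided α 0.05 and 80% power. HIT-6: "The migraine HIT-6 score was 66.2 ± 5.1" and "Migraine scale HIT-6 score decreased by 1.5 points". Migraine days: "the frequency of migraines treated with medication was 6.5 ± 2.4 days/month" and "The frequency of migraine was expected to decrease by 0.6 days in PFO occlusion group". 220 per group, allowing for 20% loss.

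**Assumptions.** The correlation r between baseline and follow-up is not given; 0.3 to 0.7 is shown. The SDs are taken as follow-up SDs, equal at baseline. The 0.6 days is taken as the difference between groups.

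**1. Reproduce the plan's driving figure.** For HIT-6, n = 2(1.96 + 0.842)² × (5.1/1.5)² ≈ 182 per group. The t-based value is 182.4, rounded up to 183, which is the stated figure. The plan was thus sized as an unadjusted two-sample comparison. Then 183 × 1.2 = 219.6, giving 220, and 220 × 0.8 = 176 per arm remain after 20% loss.

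**2. Migraine days, 176 per arm, difference 0.6.** The SD that drives the comparison is:

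- follow-up values alone: 2.4
- change score: 2.4 × √(2(1 − r))
- ANCOVA on baseline: 2.4 × √(1 − r²)

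Two-sample t power:

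| r | SD, ANCOVA | Power, ANCOVA | SD, change | Power, change | Power, follow-up only |
|---|---|---|---|---|---|
| 0.3 | 2.29 | 68.9% | 2.84 | 50.7% | 64.8% |
| 0.5 | 2.08 | 77.1% | 2.40 | 64.8% | 64.8% |
| 0.7 | 1.71 | 90.6% | 1.86 | 85.5% | 64.8% |

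Against the change score, ANCOVA gains about 18, 12 and 5 points. Against follow-up values alone it gains about 4, 12 and 26. At r = 0.5 the variance ratio is 0.75 against either, equivalent to 1/0.75 = 1.33 times the patients. If 2.4 were instead the SD of the change, the ANCOVA variance would still be (1 + r)/2 of it: 0.65, 0.75 and 0.85.

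**3. HIT-6, the outcome that set the sample size.** With SD 5.1 × √(1 − r²), the n needed falls from 182 to 166, 137 and 93 per group. Power at 183 rises from 80.3% to 83.9%, 90.1% and 97.6%.

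**4. What selection by significance does.** A simulation used 183 per group and ten candidate covariates, with baseline correlated 0.5 with the outcome and three others 0.15. All these inputs are assumed; there were 4,000 null data sets. Type I error:

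| Analysis | Type I error |
|---|---|
| Unadjusted | 5.1% |
| Fixed baseline ANCOVA | 5.0% |
| Covariates selected by significance, applied once | 5.1% |
| Better of unadjusted and selected | 7.7% |
| Best of all models tried | 10.1% |

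Monte Carlo error is about √(0.05 × 0.95/4000) = 0.3 points, so the first three do not differ. Inflation comes from picking among models. Power at the HIT-6 effect (2,000 data sets) was 80.7% unadjusted and 89.8% with fixed baseline ANCOVA.

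**5. Complete cessation.** No rates are given, and a yes/no cessation outcome has no baseline value of its own. No gain can be computed.

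**The case against.** The strongest reply is that the covariance sentence governs only an additional analysis. The primary endpoint is compared by chi-square in the intention-to-treat set, with no selected covariates, and unadjusted tests are valid in a randomised trial. This stands: nothing in the article lets an adjusted model replace the main result.

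A reader might infer that the adjusted p-values and intervals are invalid. The check does not support this for type I error, which selection applied once leaves at about 5%. The article does not say that the best of several models will be reported; it only fails to rule that out.

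A reader might also infer that baseline is ignored. For the secondary efficacy endpoints it is not: both reductions and the responder rate are measured from baseline. It is used inefficiently, and the fair comparator for migraine days is the change score rather than follow-up values alone.

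The diagnostic entry criterion ("Subject is diagnosed of migraine without identifiable cause of headache") and the rest of Table 1 set no minimum migraine frequency. It is tempting to conclude that baseline frequency will vary widely and strongly predict cessation. The article gives neither a baseline distribution nor any prognostic strength. Variation much wider than planned would also make 2.4 too small for the powers above.

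The wording could be read as meaning known prognostic factors, and an article may leave the list of covariates to the full plan. The absence of a list is not the point here. The point is the stated criterion, for which selection on observed significance is the likelier reading. Finally, centre is already a random effect and aura already a predefined subgroup, so part of the remedy is in place.

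**Conclusion.** The point holds as an inexpensive improvement; it does not make the main analysis wrong. The covariance sentence allows a data-driven covariate set in an additional analysis, and the continuous outcomes are compared without covariates although baseline is needed for the change and responder endpoints.

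For migraine days, ANCOVA is worth about 5 to 18 points of power over a change-score t-test across the assumed correlations, and it is the most powerful of the three options at each of them. These figures rest on the assumed r, on 2.4 as a common SD at both times, and on 0.6 as the between-group difference. They concern a secondary endpoint. That this endpoint is short of 80% power before adjustment is a sample-size matter: 0.6 and 2.4 require about 252 per group, against the 113 stated. It should not be put down to the lack of covariates.

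For complete cessation the document supports no estimate of gain and gives no compelling reason to displace the chi-square test.

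**What to change.** Before outcome data are compared by arm:

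- Replace the covariance sentence with a prespecified set: the baseline value of the outcome, aura, and centre as a random effect. Delete selection by significance.
- Make ANCOVA or a mixed model on that set the analysis of monthly migraine days, attacks, HIT-6 and SF-36v2. With baseline as a covariate, a linear model gives the same treatment effect whether the response is the follow-up value or the change, so the reduction endpoints keep their meaning. The t or Wilcoxon comparisons can remain as sensitivity analyses.
- Keep the chi-square test for complete cessation. Add a prespecified logistic model with baseline attack frequency as a supporting analysis.

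The cost is a change of wording in the protocol and analysis plan and slightly more analysis work. No new data, visits or patients are required.
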